
#### Health and Well-being (all assessments)

Several objective and subjective measures regarding health and well-being will be also administered to complete assessments of correlates of exercise. These measures will include generic [86, 87] and menopause-related health-related quality of life [88], perceived health status (single-item indicator, 0 = the worst possible to 10 = the best possible) [89], lifestyle health-related behaviours [76], motives, expected benefits, beliefs and attitudes towards exercise (*ad-hoc* self-report adapted to middle-aged women based on previous published questionnaires [90], subjective well-being [91] and cardiometabolic health indicators. The latter consist of both structural (e.g., objective BMI and body composition using bioelectrical impedance analysis) and functional indicators (e.g., heart functioning, aerobic aptitude index) as well as fitness indicators [92]. These measures are fully described elsewhere [93, 94].

By measuring these predictors, correlates and outcomes, we will gather the required information on personal and interindividual differences across multiple domains of variables related to exercise. Additionally, we will gain insights into contextual factors that are likely to shape health-related and active behaviours among postmenopausal women. Figure 2 provides an overview of all measures and the corresponding time points for data collection throughout the study.

**Fig. 2 Fig2:**
[figure not shown]
SPIRIT timeline of enrolment, interventions and assessments

### Procedures

The study will be publicised through several channels (e.g., media advertisements, online social networks, institutional e-mailing, gynaecology outpatient clinics, women’s associations, gyms, fitness clubs, community and university exercise programmes, neighbourhood associations, other community resources, snowball sampling) to recruit a wide sample of postmenopausal women interested in participating, along with information on how to contact the researchers (an e-mail and a telephone number). Once potential participants contact the research staff, they will be required to attend an informative session where they will receive detailed information about the general goal and procedures of the study, their rights and tasks as participants and topics such as the confidentiality of their responses and the exclusive use of data for scientific purposes. During this meeting, participants will be encouraged to express any doubts or concerns and to consult with the research staff. After agreeing to continue with enrolment, participants will be asked to sign an informed consent form. A research assistant will then contact each participant to schedule two lab visits for the first assessment phase, which will include a face-to-face clinical interview, the self-report-based evaluation conducted through an online survey implemented using an open access resource such as Limesurvey (Limesurvey GmbH, Hamburg, Germany) [95] and the remaining measures that need to be completed (e.g., weight, fitness tests). Baseline measurement will be conducted with all the women to screen eligibility criteria and collect pre-intervention data.

Upon meeting the eligibility criteria, the final study sample will be allocated to an intervention group receiving the intervention (*n* = 100), a control group of sedentary women (*n* = 100) and a control group of regularly active women (*n* = 100). The non-active participants will be randomly allocated to two groups: the intervention group and the sedentary control group, making this a randomised controlled arm of the study. This random allocation will be performed by, for example, computer-generated random numbers. The sedentary control group will be considered a waiting list group. On the other hand, women who already engage in regular exercise will be assigned to the active control group. Since these women are already active, this will be a non-randomised controlled arm of the study.

### Intervention

A three-component intervention will be offered, which includes:

A multicomponent, supervised exercise programme with a 3-month (12 weeks) minimum duration will be offered to the intervention group. The exercise programme will consist of three 1-h weekly sessions on alternate days. Participants will be able to choose from several schedules available in both the morning and afternoon periods. The programme will be designed and implemented by experts in Exercise and Sport Sciences and Sport and Exercise Medicine, following international recommendations for exercise in middle-aged women [96, 97]. The programme will include training for aerobic cardiorespiratory fitness, muscle resistance, as well as other fitness functions including flexibility, coordination and balance. Hence, it will meet the required conditions in terms of activity type, duration, frequency and intensity parameters and principles and methodology of training for a healthy, safe, successful and enjoyable practice for adult women, thus being suited to their characteristics and needs for maximising benefits while minimising risks. The programme will be implemented in supervised group classes conducted in a gym facility (e.g., in the university campus). To assess adherence to the programme, objective tracking measures will be utilised, including attendance monitoring. All these features are designed to optimise participation as well as outcomes. Additionally, a health insurance policy will be put in place to cover any potential risks and provide necessary medical assistance if required.A simultaneous intervention focusing on self-management of behavioural change, based on the tenets of the HAPA model, will be offered throughout the duration of the exercise programme. This intervention has been designed based on previous HAPA-based interventions [98–103]. To summarise, the intervention will provide information on the benefits of an active lifestyle and exercise, specifically for postmenopausal women, addressing risk perceptions and outcome expectations while facilitating the creation of an intention (Session 1). The participants will be also educated on the key factors for adopting and maintaining an active behaviour, such as identifying barriers and facilitators, basic self-monitoring and self-management skills for action regulation (e.g., self-monitoring, self-reinforcement, setting a daily time schedule, emotional regulation, seeking social support and reinforcement from significant others); these elements contribute to improving motivational action self-efficacy (Session 2). The subsequent 3 to 5 sessions will focus on motivational determinants of exercise initiation, including goal setting (behavioural intention), action planning and pre-actional/task self-efficacy to improve motivation and action initiation. Sessions 6 to 9 will address volitional determinants of maintaining adherence, covering self-regulatory skills including action and maintenance plans for autonomous exercise, maintenance and coping self-efficacy and relapse management (i.e., risk identification, functional responses and coping skills training). A final session is devoted to summarising the personal progress of the participants with this intervention. The aim of this intervention is to ensure that women not only adhere to the supervised exercise programme offered within the study, but mainly to promote long-term, self-managed adherence to the newly established lifestyle beyond the completion of the supervised exercise programme. To achieve this, the adherence promotion intervention will be delivered during the entire implementation of the exercise programme, divided into two phases according to the process of behavioural change. During the first phase of the programme, the focus will be on addressing issues pertaining to initiation and short-term maintenance. Researchers and implementers will play a central role in providing external regulation and support as a strategy to facilitate adherence. During the second phase of the programme, the emphasis will shift toward long-term maintenance. Building on the knowledge and skills acquired by the participants, the intervention will promote the transition to self-regulation and the development of intrinsic motivation based on enjoyment and personal growth.

During the interventions described in 1) and 2), attendance to the exercise programme will be monitored by the trainer. Regular updates will be provided to the participants by the researchers and will serve as a basis for working with the behavioural change intervention.

3)A health education and promotion intervention (15 60-to-90 min. sessions) designed and implemented by experts in women’s health, will also be offered. This will focus on providing information and recommendations regarding a healthy lifestyle during postmenopause. The issues covered will include healthy eating and weight management, sexuality and intimate relationships, family and social support, social activities, emotional self-regulation, body appearance management and body image, unhealthy habits such as tobacco and alcohol use and other health-related behaviours (e.g., sleep, leisure time habits). This intervention will also be offered on a voluntary basis to the participants in the control groups to ensure equal treatment among the study groups in terms of lifestyle after menopause (except for active behaviour). Health education is typically provided as standard care in menopause and postmenopause (e.g., EMAS Consensus Statement [82].

After the multi-component intervention, measurements will be repeated at post-intervention and follow ups. All the measurements will be conducted to ensure that the evaluators are blinded to the participants’ allocation to the study groups (e.g., online survey). 

To encourage adherence to the procedures, various strategies will be implemented, including the provision of regular feedback on attendance to the exercise programme and sending reminders to participants regarding the assessment phases. Additionally, in cases of non-compliance, motivational inquiry will be conducted through open and supportive dialogue to address the underlying reasons and to ensure compliance. Nevertheless, disengagement can offer interesting information, and the non-adherent participants will not be excluded from the study or analyses. 

Figure 1 illustrates the stages, planning and distribution of the research activity as well as the flow of the current study procedures. The timeline of the procedure is described as a SPIRIT figure in Fig. 2.

Ethical approval has been obtained from the Ethics Committee on Human Research of the University of Granada (Spain), reg. B-CTS-342-UGR20 (2021–23), on November 17, 2021. Written informed consent will be obtained from all the participants. All procedures will be conducted in accordance with the ethical principles for research involving human subjects detailed in the Declaration of Helsinki and updates. Study participation will be voluntary. Reasons for withdrawal may include exercise-related injuries, significant changes in health status, hormone therapy recommendation or the participant’s personal request to withdraw or refuse consent at any time during the study.

The study protocol has been pre-registered at BMC ISRCTN registry (ISRCTN16251361).

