To test the HAPA tenets in middle-aged postmenopausal women while filling the abovementioned gaps in the literature, the main aim of this study is two-fold. First, we aim to explore the influence of the social-cognitive variables relevant at each stage of the process of behavioural change based on HAPA predictions, and second, to test the goodness of fit of the model for exercise behaviour among women in early postmenopause (up to ten years after menopause). Specifically, the sub-aims of the present study protocol are the following:To explore the HAPA constructs at every stage of the change process in new exercisers, that is participants adhering to exercise practice while simultaneously receiving an intervention based on the HAPA model (Intervention group). These will be compared with regularly active (active control) and non-active (sedentary control) postmenopausal women, all with different socio-demographic, personal and clinical characteristics. Consequently, this sub-aim has the following specific objectives:to determine changes in the HAPA variables in the intervention group throughout the study phases, and in this regard:H1: we hypothesise that there will be a significant improvement in both intentional-motivational and postintentional-volitional variables in the participants in the exercise programme supplemented with the HAPA intervention.to compare the intervention, sedentary and active groups across the motivational and volitional phases of the HAPA model, and in this regard:H2: we hypothesise that, at baseline, non-active women (i.e., sedentary and intervention groups) will show similar HAPA determinants of exercise intention, while the active controls will obtain more positive results in the HAPA motivational constructs, andH3: we hypothesise that, at post-intervention and subsequent follow-ups, the new exercisers and the active women will show similar HAPA self-regulatory skills of the volitional-actional stage but will differ significantly from the sedentary women.To explore whether the HAPA constructs at the different stages of the process of behavioural change — i.e., non-intention, intention, action and disengagement — and phases of the process, that is, motivational (preintention) and volitional (intention-action-adherence), predict the adoption of exercise behaviour among postmenopausal women. In this regard:H4: we hypothesise that while the HAPA model will be applicable to this population, supporting its main predictions, adjustments in the model predictions will be necessary to optimise its explanatory power, considering the experiences, resources and opportunities of middle-aged women, andH5: personal (i.e., fitness status, physical and mental health status and sociodemographic variables) and clinical factors (i.e., menopausal manifestations and menopause-related quality of life) will intersect with HAPA variables in the prediction of exercise behaviour and behaviour change, supporting the existence of phenomena that are pertinent and exclusive of middle-aged women and are grounded in their experiences, realities and needs.

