
## Methods

### Study design

This project is designed as a longitudinal prospective, multi-design study, incorporating both a randomised controlled study (for intervention and sedentary participants) and a non-randomised controlled study (for intervention/sedentary and regular active participants). The study will utilise between-group (intervention, sedentary and active participants) and within-subject measures (baseline, post-intervention and 1- to 12-month follow-ups) (see Fig. 1). The Intention-to-treat methodology, considered the gold standard for RCTs [69, 70], will be implemented to ensure that data from the participants in each assessment phase fit with the inclusion criteria of each study group, with the aim of preventing interferences caused by unexpected changes over time in their assigned condition (e.g., an active women withdraws regular practice due to injury; or a sedentary woman is motivated to autonomously become an exerciser). Moreover, this approach will help to mitigate the potential reduction sample size and loss of statistical power resulting from participant attrition.

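### Injury, health change and a hormone-therapy recommendation are listed as withdrawal reasons without saying whether outcome assessment continues, which overlaps with the rule that keeps non-adherent women

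*Protocol article*

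**What the plan says.** Four places in the protocol article bear on this point.

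- **Intervention, ethics paragraph.** "Reasons for withdrawal may include exercise-related injuries, significant changes in health status, hormone therapy recommendation". The same sentence then adds, as a separate item, the participant's "personal request to withdraw or refuse consent at any time during the study".
- **Intervention, paragraph on adherence.** "disengagement can offer interesting information, and the non-adherent participants will not be excluded from the study or analyses".
- **Study design.** What is called intention-to-treat is meant "to ensure that data from the participants in each assessment phase fit with the inclusion criteria of each study group". One example of an interference to be prevented is that "an active women withdraws regular practice due to injury". The same paragraph also expects the approach to limit loss of sample size through attrition.
- **Aims and hypotheses.** The second sub-aim studies HAPA constructs across the stages, "i.e., non-intention, intention, action and disengagement". H5 uses "fitness status, physical and mental health status and sociodemographic variables" as personal factors and states that "clinical factors (i.e., menopausal manifestations and menopause-related quality of life) will intersect with HAPA variables in the prediction of exercise behaviour".

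Data management and analyses handles missing data by pairwise deletion or, where feasible, by last observation carried forward. The latter is illustrated with control participants whose condition has not changed.

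**The concern.** Injury, a change in health and a hormone-therapy recommendation can all be expected in early postmenopausal women followed through a programme of at least 12 weeks and then for 12 months. They are also plausible reasons for stopping exercise. If they lead to withdrawal from follow-up, the women lost are not a random subset, because the loss is linked to the behaviour being measured.

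Two things are at stake. First, the trial wants to observe disengagement, and disengagement caused by injury or ill health is part of it. Second, an exercise injury requires exercise, so that loss would fall mainly on the intervention and active groups and little on the sedentary controls. That would make follow-up unequal in the comparisons for H3, including the randomised one. Follow-up that was never collected cannot be recovered at analysis.

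**Working it through.** **Setting the statements side by side.** Take a randomised woman who is injured in week 8 and stops exercising.

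1. Under the adherence paragraph she is non-adherent, and she stays in the study and the analyses.
2. Under the ethics paragraph her injury is a listed reason for withdrawal. Because personal request is a separate item, the decision need not be hers. The preceding sentence concerns study participation, so withdrawal from the study is a natural reading, though not the only one.
3. Under Study design, data at each phase should match the entry criteria of her group. The injury example there concerns an active control, but it points the same way: stopping through injury is treated as an interference.
4. Nothing in the article says which statement prevails, or whether she still completes the surveys.

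**Whether the missing-data methods repair it.** Pairwise deletion leaves out the unobserved low-activity values. Last observation carried forward is justified in the text by an unchanged condition, which an injured woman does not have. If it were applied to an injured active control, it would carry her pre-injury exercise level forward.

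**The plan's own figure.** The dropout allowance reproduces: 80 / (1 − 0.20) = 100 per group.

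**Illustrations. All rates are assumed, because the protocol gives none.**

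(a) *Observed disengagement.* Let D be the true rate and s the share of disengagers who are withdrawn and unobserved. The rate among women still observed is D(1 − s) / (1 − D·s).

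- D = 0.30, s = 0.10: 0.27 / 0.97 = 27.8%
- D = 0.30, s = 0.40: 0.18 / 0.88 = 20.5%
- D = 0.50, s = 0.10: 0.45 / 0.95 = 47.4%
- D = 0.50, s = 0.40: 0.30 / 0.80 = 37.5%

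(b) *Mean exercise in the intervention arm.* If a share w is withdrawn and would have exercised 150 min/week less than the rest, the mean of those remaining exceeds the full-arm mean by w × 150. For w = 0.05, 0.10 and 0.15 this is 7.5, 15 and 22.5 min/week. The gap of 150 is severe: supervised exercise totals 3 × 60 = 180 min/week, so it means almost complete cessation in every withdrawn woman. The figure carries over to the difference from sedentary controls only if they lose nobody for these reasons. That is plausible for exercise injury but not for the other two.

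(c) *Power.* Eighty per group gives 80% power (two-sided 5%, assumed) at a standardised difference of (1.960 + 0.842) × √(2/80) = 0.443. The protocol states neither this difference nor the sidedness. If these withdrawals came on top of the 20%, a further 5 to 20 percentage points would leave 75 to 60 per group, with power of 77% to 68%. If they fall within the 20%, power is unchanged.

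**The case against.** The case on the other side is substantial.

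- **The list is permissive.** It says what reasons may include, in an ethics paragraph about voluntary participation. A reader might infer that women with these events must be withdrawn; the text does not say so. This stands. Discretion does not remove the problem, however, since it lets staff decide who leaves follow-up after an event linked to the outcome.
- **Disengagement is already protected.** The adherence paragraph keeps non-adherent women, plans inquiry into their reasons, and provides reminders. A reader might infer that disengagement is removed from the data altogether. The documents do not support that: at most the part linked to injury, health or hormone therapy is exposed, and only if those women also leave assessment.
- **H5 could be misread.** A reader might infer that H5 sets out to explain symptoms, and that symptom data are lost. In fact H5 uses health status and menopausal manifestations as predictors of exercise behaviour. Health and well-being measures are planned at all assessments, and no text discards data collected before withdrawal. This stands.
- **Hormone therapy has a rationale.** Recent use is an entry exclusion, so listing a recommendation as a withdrawal reason is not arbitrary. It is also only an indirect marker of symptom burden. This stands.
- **The article is condensed.** The full protocol may separate leaving the programme from leaving assessment. That is fair, and silence on this alone would not be a point. What remains is that the article's own statements overlap and give different answers for the same woman.

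**Conclusion.** The concern holds in a limited form. The ethics paragraph allows withdrawal for three events apart from the woman's own request, and this is not reconciled with the retention of non-adherent women or with the Study design paragraph. If women with these events leave follow-up, some disengagement goes unobserved. For exercise injury the loss would fall mainly on the exercising groups, and neither planned missing-data method corrects for it.

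The size is unknown. The illustrations rest on assumed rates, an assumed gap of 150 min/week, and the assumption that withdrawn women are not assessed further. A reader might infer that the trial will understate both disengagement and the H5 associations. That goes too far: health changes and hormone-therapy recommendations can arise in all three groups, so the direction of any bias from them is undetermined. The point is a worthwhile, low-cost improvement, not a flaw that invalidates the design.

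**What to change.** Reconcile the Study design paragraph, the adherence paragraph and the ethics paragraph so that they give one answer. Specifically:

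- State that injury, a change in health or a hormone-therapy recommendation does not by itself end outcome assessment, and that only the woman's own withdrawal of consent does.
- Continue the IPAQ and HAPA surveys, already planned online, at the remaining time points, whatever is decided clinically about exercise or treatment.
- Record the event and its date, so that it can be used as a reason for disengagement in the second sub-aim.
- Keep randomised women in their assigned group in the randomised comparison.

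This sets no rule on who should exercise or be treated. The cost is protocol wording and use of reminders that are already planned. The downsides are a slightly less favourable adherence estimate, and the need to record hormone-therapy use and show its influence in a sensitivity analysis.
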